### Blinding

The statisticians and senior investigators will be blinded to the arm allocation. Field staff involved in intervention or control delivery and assessments will not be blinded. Participants will not be blinded to study arm allocation.

### Intervention co-development

Before commencing the pilot CRT phase, a co-development phase was conducted. Three participatory workshops were conducted with a group of women caregivers of CALHIV from an existing caregiver advisory board (CAB). Led by Project Empower, a local feminist community-based NGO, these workshops facilitated the adaptation of the SSCF curriculum and training manuals to center the needs and preferences of the caregivers in the curriculum, training, implementation, and evaluation of the manuals and questionnaires. The gender analysis matrix [26], a participatory approach to intervention development that supports women in challenging gender assumptions constructively, was applied to ensure women’s needs were met and incorporated into the adaptation of SSCF. Investigators met regularly over a 2-month period to revise session manuals. Thereafter, a brief pre-test of the adapted workshop and data collection instruments, including the baseline and endline questionnaires, was conducted with a sample of caregivers. From this pre-test, the adapted workshop and data instruments were future refined and finalized.

### Intervention

Participants randomized to the intervention arm will receive a monthly ZAR350 (USD $18.79) cash transfer in addition to 10, 3-h face-to-face adapted SSCF workshop sessions over a 6-month period to assess the additional benefit of a short SSCF intervention irrespective of a monthly cash transfer. The workshops will be facilitated at the trial office by experienced facilitators from Project Empower. Topics featured in the workshops include maintaining positive mental health and wellbeing, parenting, caregiving for CALHIV, managing HIV-related stigma and HIV disclosure, and potential ways to effectively utilize the cash transfer to meet monthly financial goals that are locally appropriate. In addition, economic empowerment themes, such as seeking employment, budgeting, savings, and economic coercion, will be included to ameliorate participants’ economic livelihoods by incorporating activities that will help improve participants’ financial circumstances, decision-making power, and self-esteem. Cash will be transferred unconditionally once a month over the 6-month period via the SAMRC (South African Medical Research Council) ABSA CashSend system, a local electronic banking service used in the CWeL trial. Participants will receive one text message from the study team containing a PIN and one text message from ABSA bank containing a 10-digit withdrawal code; both the PIN and the code will be needed to withdraw the incentive payment from an ABSA ATM.

### Proposed theory of change

This intervention is hypothesized to increase psychological wellbeing and reduce depressive symptoms and IPV through four potential mechanisms: (1) increased sense of belonging and improved management of stress through the ability to fulfill caregiving responsibilities and improvement positive mental health coping strategies; (2) increased self-worth and agency through increased financial efficacy, engagement in income generation or saving activities, and increased decision-making power in relationships; (3) improved awareness of gender inequities and harmful gender norms; and (4) improved communication skills within relationships. See Additional file 4 for detailed theories of change from the CWeL and SSCF trials that have informed this trial [27].

### Control

Participants in the control arm will receive a monthly ZAR350 (USD $18.79) cash transfer for a 6-month period along with a once-off SMS at the beginning of the trial, encouraging them to access routine public sector healthcare services at their nearest government clinic. Cash will be transferred to control arm participants in the same manner as intervention arm participants.

### Qualitative study

Ten caregivers from each arm will be purposively sampled to complete semi-structured in-depth interviews (IDIs) at the start and end of the trial to better understand the lived experiences of caregivers pre- versus post-COVID- 19, perceptions of the intervention and control, and how the intervention may have shaped caregiver wellbeing [28]. Interviews will be guided by an intersectional framework to identify differing experiences of caregivers based on varying positionalities including household socio-economic status, age, ability, and HIV status, and how prior adverse events that may reoccur intersect to impact wellbeing and possible methods through which the intervention works to shape wellbeing. IDIs will be conducted by an experienced qualitative research assistant from the CWeL pilot trial, at baseline and endline, in participant’s preferred language. All interviews will be audio-recorded and based on a semi-structured interview guide that will feature open- and close-ended questions. Key themes from the qualitative data will be routinely shared with investigators for reflection and suggestions on further areas to probe. Refer to Fig. 1 for a visual representation of the study design.

### Economic evaluation

An economic evaluation will be conducted alongside the trial using a micro-costing approach to assess the financial and economic costs of the project from a societal perspective [29]. Cost estimates of staff time, design, training, supervision, workshop sessions, and cash transfers will be conducted in detail. Costs will be treated as either fixed or variable costs. Fixed costs will mainly consist of all study startup costs for vehicles, furniture, and equipment. Variable costs will include (1) consultation costs for developing and finalizing the training manual, (2) operational staffing for running workshops and cash transfers (3), utilities (e.g., rent, water, and electricity), and (4) supplies used in the workshops. Participants’ indirect costs for attending the workshops will also be estimated. These will include transport costs and carer costs. All other inputs will be considered as overheads and calculated using a step-down approach. Cost estimates will be obtained from the project’s financial documents and a time-and-motion study will be conducted to accurately value staffing time spent delivering the workshops.

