### Ethical considerations

Voluntary written informed consent will be obtained from participants prior to participation in the participant’s preferred language. Ethics approval for this trial has been granted from the SAMRC Human Research Ethics Committee (EC006 - 2/2023), the KwaZulu-Natal Department of Health (KZN DoH) (KZ_202304_010), and Simon Fraser University (30,001,806), a key collaborating institution. All participants will be reimbursed at least R150 for each physical interaction with the study team (i.e., baseline and follow-up surveys, workshops, and qualitative interviews). This amount will be for their time (i.e., R50), transportation (R50), lunch (R50), and carer costs (If applicable, will be treated on a case-by-case basis).

The trial is subject to the following ethical considerations. Notably, given the sensitive nature of certain questions or modules, there is the potential risk of participant discomfort or distress. To minimize this risk, female fieldworkers with a background in GBV research and HIV counseling have been hired. Additionally, fieldworkers have been trained to identify early signs of discomfort or distress, and counsel and link participants to appropriate care accordingly. Further, there is the potential to identify victims and perpetrators of abuse throughout the screening and workshop procedures. The study team will adhere to reporting requirements of the Children’s Act of 2005—Sect. 110 in the case of reported or suspected child abuse [47]. Additionally, a referral system will be implemented to ensure vulnerable groups or participants who have disclosed experiences of GBV or abuse are linked to local health care and social services that can adequately respond. Informed consent forms will highlight the procedures, with fieldworkers assuring participants that their confidentiality will be respected but managing expectations.

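### The societal costing gives participants' workshop time (30 session hours per woman, intervention arm only) no stated place or valuation

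*Protocol article*

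**What the plan says.** The Economic evaluation section sets out to "assess the financial and economic costs of the project from a societal perspective". For the women who attend, it says that their "indirect costs for attending the workshops will also be estimated. These will include transport costs and carer costs". The only stated method for valuing time concerns employees: "a time-and-motion study will be conducted to accurately value staffing time spent delivering the workshops". The remainder is assigned by a general rule: "All other inputs will be considered as overheads and calculated using a step-down approach". Cost data come from the project's financial documents. The study timeline also shows cost interviews at baseline and endline.

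The Intervention section fixes the participant input at "10, 3-h face-to-face adapted SSCF workshop sessions over a 6-month period". The Control section contains no workshops, and the cash transfer is the same in both arms.

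Under Ethical considerations, "All participants will be reimbursed at least R150 for each physical interaction with the study team", workshops included. On its make-up the article says: "This amount will be for their time (i.e., R50), transportation (R50), lunch (R50), and carer costs", with carer costs decided case by case. The Economic evaluation section does not mention these reimbursements.

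**The concern.** In an economic costing from a societal perspective, time that participants give up is a resource whether or not anyone pays for it. Here the staff hours in the workshop room are to be measured and valued. The women's hours in the same room are given neither a line nor a method. The residual rule does not help: a participant's time is not an organisational overhead and cannot be derived by step-down allocation.

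The protocol elsewhere recognises this time as a cost, since it pays for it. Of time, transport and carer costs, all of which are reimbursed, the Economic evaluation section names transport and carer costs and leaves time unnamed.

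Cost and cost-effectiveness are a stated objective, and the secondary outcomes include an average cost per participant with improved wellbeing in each arm. Because cash is equal across arms, the workshops are what separates the arms' costs. An input present in one arm only, with no rule for counting it, falls directly on that difference.

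**Working it through.** The article gives no participant time cost and no total cost, so there is no plan figure to reproduce. The check sets the two sections side by side and then sizes the item.

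**Where each participant item appears**

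| Item | Economic evaluation | Ethical considerations (per contact) |
|---|---|---|
| Transport | named | R50 |
| Carer costs | named | case by case |
| Participant time | not named; no valuation method | R50 |
| Lunch | not named | R50 |
| Staff time | time-and-motion study | not applicable |

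**Hours** (Intervention section; planned arm size 120; 149 at baseline under Trial status)

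- Per woman: 10 × 3 h = 30 h, excluding travel.
- 120 women: 120 × 30 = 3,600 h. 149 women: 149 × 30 = 4,470 h. Control arm: 0 h.

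**Value at the protocol's own rate, full attendance**

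- R50 / 3 h = R16.67 per session hour.
- Per woman: 10 × R50 = R500, about USD 26.8 at the article's rate (500 × 18.79 / 350).
- 120 × R500 = R60,000; 149 × R500 = R74,500.

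**Sensitivity (assumed inputs, not in the article)**

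- R10 to R25 per hour with 0 to 2 h travel per session: from 10 × 3 × R10 = R300 to 10 × 5 × R25 = R1,250 per woman. The upper end combines the highest rate with the longest travel.
- Attendance of 60% to 100% at R50 per session: R300 to R500 per woman.

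**What happens under each treatment of the reimbursements** (per woman, full attendance)

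1. Left out as transfers, with participants' transport and carer costs added: time is missing, and the societal cost is about R500 too low.
2. Booked as project cost, with only unreimbursed transport and carer costs added: nothing is counted twice, and time enters at a flat R50 per session with no separate allowance for travel time.
3. Transport and carer costs taken from the reimbursement records themselves: each is counted once; time enters only if its R50 is taken up as well.
4. Booked as project cost, with gross transport and carer costs added on top: transport is counted twice, by up to 10 × R50 = R500, plus a carer amount that cannot be computed.

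The article does not say which applies. Treatments 1 and 4 err in opposite directions.

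**The case against.** The strongest reply is that this is a condensed article and the list is not closed. The participant costs are introduced with the word *include*, which is not *only*, and nothing states that time is excluded. Costs and earnings are collected by questionnaire, cost interviews are planned and costing workbooks exist; none of these instruments is shown. The cost outcomes are stated per arm, and total provider cost does not depend on participants' time at all.

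Much of this stands. A reader might infer that the societal total must be wrong whichever way the section is read, because either time is dropped or transport and carer costs are counted twice. The documents do not support that. Double counting is stated nowhere and needs two assumptions: reimbursements booked as project cost, and gross participant costs added to them. Treatment 2 avoids double counting and captures time at R50 per session, and treatment 3 can do the same; the article excludes neither. Nor should R500 be read as a share of the R2,100 cash transfer (6 × R350), which both arms receive and which is not the cost of the workshops.

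The appeal to condensation does not dispose of the point. The article is not merely silent: it fixes the perspective, names the participant items, confines time valuation to staff and assigns the remainder to overheads. Followed as written, that scheme leaves participants' time without an opportunity-cost valuation.

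**Conclusion.** The point holds as a gap between the declared perspective and the stated cost list. Participants' time, 30 session hours per woman in the intervention arm only, has no stated place or value in the societal costing, while another section of the same article pays for it.

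Unless the time enters through the booked R50 payment, the intervention arm's societal cost is understated by about R500 per woman, or R60,000 for 120 women and R74,500 for 149. This assumes full attendance and the protocol's own R50 per session; on the assumed ranges for hourly value and travel it is R300 to R1,250 per woman. The proportion of total workshop cost is unknown, because facilitator, staff, rent and supply costs are not given. Transport and carer costs could be counted twice under one accounting treatment, but this is conditional and has not been shown. The provider-cost outcome is not affected by the omission of participants' time.

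**What to change.** In the Economic evaluation section or the costing plan:

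- Add participants' time as an economic cost: sessions attended × 3 h, plus travel time. Attendance is already to be recorded at each workshop. Ask about travel time in the endline cost interview where this is still possible (three clusters were still in workshops under Trial status); otherwise assume a range and show it.
- Value the hours from the earnings data already collected, with R50 per session as a sensitivity value. State the rate used for women who report no paid earnings, so that their time is not set to zero by default.
- State that time, transport, lunch and carer reimbursements are counted once: as payments in the provider or financial analysis, and as transfers in the societal analysis, where the participant's actual resource cost is used instead.

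The cost is a few lines in the costing plan and workbook, at most one added interview question, and a less favourable societal cost for the workshop arm.

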### Primary outcomes

#### Feasibility measures

This study trial has five feasibility measures:Pilot CRT consent rate: The proportion of eligible caregivers approached who consent to participate in the trial. For this trial, a successful consent rate will be defined as one greater than 80%.Pilot CRT overall retention rate: The proportion of participants that successfully complete both baseline and endline interviews in the intervention versus the control arm. For this trial, a successful retention rate will be defined as one greater than 85%.Intervention arm workshops retention rate: The proportion of participants that successfully attend all workshops in the intervention clusters. For this trial, a successful retention rate will be defined as one greater than 80% compliant.Cash transfer protocol adherence: The proportion of participants that successfully receive their cash transfer via the ABSA cash send system in the intervention versus control arm. Successful protocol adherence will be defined as greater than 90% compliance.Staff perceptions on project implementation: Perceived barriers and facilitators to study activities from the perspectives of field staff and facilitators (including recruitment, baseline and endline questionnaire administration, intervention and control arm delivery, retention) and strategies for improvement.

#### Potential clinical outcomes for a future trial

In addition to the feasibility measures, this study has three potential primary clinical outcomes: psychological wellbeing, depressive symptoms, and IPV. Depending on the nature of a future grant call and our pilot trial results, including our finalized theory of change model, we will select the most relevant outcome for the future larger trial.Psychological wellbeing: assessed based on the percentage change in caregiver wellbeing scores between baseline and endline in the intervention versus control arms. This will be measured using the Mental Health Continuum Short Form [30], a 14-item scale probing subjective, psychological, and social wellbeing (e.g., “In the past month, how often did you feel that you belonged to a community like a social group or your neighborhood”) [31], and the CarerQol- 7D scale, a two-part assessment of the negative and positive effects of caregiving, it includes items such as “I have no/some/a lot of fulfillment from carrying out my care tasks” [32].Depressive symptoms: Assessed based on the percentage change in depressive symptom scores between baseline and endline in the intervention versus control arms. Depressive symptoms will be identified using the CES-D- 10 scale, which consists of 10 items (e.g., “During the past week, I was bothered by things that usually don’t bother me”) that assess an individual during the past week [33]. A cut-off score of 12 or higher is deemed optimal to correctly classify individuals as having probable depression for a South African sample [34].IPV: Assessed based on the difference in mean scores at endline between the intervention and control arms. Emotional, physical, and sexual IPV will be measured using the WHO’s Violence Against Women scale, which has been extensively used in South Africa [35]. The scale will be summed to create a score of severity of IPV.

#### Secondary outcomes

The secondary outcomes of this trial include: gender attitudes, examined using the 10-item Gender Role’s Belief scale to measure individual perceptions of gender roles [36]; Gender Equality Index which examines self-perceived gender equality in intimate relationships [37]; earnings in the past month, using the mean log of income generated from paid work at baseline compared to endline in the intervention versus control arm; economic empowerment scales that address financial self-efficacy, savings, control over assets, and economic coercion [35]; acceptability of the intervention package and delivery in the intervention versus control arm; total provider cost of intervention delivery; total direct and indirect costs associated with caregiving; and the average cost per participant with an increase in wellbeing score in each arm.

See Additional file 5: Table S1 for a detailed summary of primary clinical outcomes and secondary outcomes.

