
### Objectives

To co-develop a gender transformative economic empowerment intervention and a cash transfer to women caregivers of CALHIV.To assess the feasibility of this intervention in terms of key trial processes in the intervention and control arms.To describe participants’ views on the acceptability of delivery, content, safety, and utilization of the intervention versus control activities.To understand the mechanisms through which the intervention works to improve psychological wellbeing, economic empowerment, and experiences of gender inequity.To estimate the potential effect size of this intervention on key indicators to inform future trial design (improvements to psychological wellbeing, positive gender attitudes and earnings, and decreases in depressive symptoms and IPV) amongst caregivers of CALHIV.To measure the cost and cost-effectiveness of this intervention.

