### Statistical analysis

All statistical analysis will be performed using Stata V18.0 [38]. Baseline participant characteristics will be presented using descriptive statistics, including means, medians, and interquartile ranges. Feasibility outcomes will be analyzed using simple descriptive statistics (proportions) and results compared by arm. Linear mixed-effects models will be used for endline scores, adjusting for baseline scores and clustering. To account for the small number of clusters, the Satterthwaite correction will be applied to adjust the degrees of freedom in the linear mixed-effects models [39]. For all binary outcomes, depending on the prevalence of the outcome, we will use mixed effects logistic regression for prevalence less than or equal to 10% and log-binomial or robust Poisson regression when the outcome is common. The number of participants who completed baseline and endline interviews and attendance will be ascertained at each workshop to determine the retention rate.

For the economic evaluation, a breakdown of the total financial and economic costs for key cost categories will be presented to assess the feasibility of the trial, stratified by arm. The average cost per participant will be presented by the outcome. Costs will be presented in 2023 ZAR and USD and adjusted for inflation.

For the qualitative study, electronic audio files will be transcribed and verified by a study team member. A codebook will be developed and transcripts will be coded, with codes grouped into categories and, in turn, themes [40]. An intersectional analysis of the experiences of caregivers will be conducted by heeding stories of the ways intersecting identities shaped experiences during the pandemic [41]. Qualitative data will be used to illuminate preliminary patterns identified in the quantitative data and probe feasibility measures for the trial.

The team of investigators will be consulted to assess whether the hypothesized theory of change [27] was supported by the quantitative and qualitative data and to determine staff perceptions on project implementation; this will allow for the theory of change to be refined and strengthened and to assess the feasibility of the trial (see Table 1 for the study timeline).

**Table 1 Tab1:** Study timeline

	**Months 1–3**	**Months 4–6**	**Months 7–9**	**Months 10–12**	**Months 13–15**	**Months 16–18**	**Months 19–21**	**Months 22–24**

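### The only measure joining cost and effect is a per-arm average cost per participant with any wellbeing increase, which cannot answer the cost-effectiveness objective

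*Protocol article*

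**What the plan says.** The Objectives include "To measure the cost and cost-effectiveness of this intervention". The Intervention section frames the contrast as incremental: the workshops are added "to assess the additional benefit of a short SSCF intervention irrespective of a monthly cash transfer", and the Control section gives the other arm the same monthly ZAR350 for six months.

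The one outcome that combines cost and effect is listed under Secondary outcomes: "the average cost per participant with an increase in wellbeing score in each arm". The Statistical analysis section stays with averages: "The average cost per participant will be presented by the outcome". It also promises a cost breakdown "to assess the feasibility of the trial, stratified by arm". The article mentions no difference in cost between arms, no difference in effect set against it, and no ratio of the two.

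For psychological wellbeing, the section on potential clinical outcomes says "This will be measured using the Mental Health Continuum Short Form" and then names a second instrument, the CarerQol-7D. The cost outcome refers to a wellbeing score without choosing between them.

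The Economic evaluation section takes a societal perspective, values workshop sessions and cash transfers in detail, and estimates participants' transport and carer costs of attending. Of the rest it says "All other inputs will be considered as overheads and calculated using a step-down approach". Under Ethical considerations, "All participants will be reimbursed at least R150 for each physical interaction with the study team", workshops included. The R150 is made up of R50 each for time, transport and lunch, with carer costs handled case by case. The costing section does not mention this reimbursement.

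**The concern.** A cost-effectiveness result should show what is paid for the benefit that the intervention causes. An average ratio within one arm divides all cost by everyone whose score went up, including those who would have gone up on cash alone. Three features of the definition weaken it:

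- It is not incremental, although the design isolates the workshops.
- It sets no minimum rise, so measurement noise alone creates improvers in both arms.
- It leaves open which instrument defines improvement, so the choice could be made after the results are seen.

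The article presents the economic evaluation as filling a knowledge gap on cost-effectiveness and expects policy makers to use the results. A finite and plausible cost per improver for an intervention with no effect would mislead that audience.

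**Working it through.** The article states no cost-effectiveness figure, so there is none to reproduce. The check has three parts.

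**1. Average against incremental ratio.** Inputs from the article:

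- Cash, both arms: 6 × R350 = R2,100.
- Workshop reimbursement, intervention arm only: 10 × R150 = R1,500 for a full attender, a minimum because the article says at least R150.
- Payments for surveys and interviews, and all other delivery costs, are set to zero for illustration.

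Intervention cost is then R3,600 and control cost R2,100. The average ratio is cost ÷ proportion improved, within an arm. The incremental ratio is (3,600 − 2,100) ÷ (p1 − p0). The proportions improved are assumptions.

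| Improved, intervention v control | Average, intervention | Average, control | Incremental, per additional improver |
|---|---|---|---|
| 50% v 50% | 3,600/0.50 = R7,200 | 2,100/0.50 = R4,200 | 1,500/0, undefined |
| 55% v 50% | 3,600/0.55 = R6,545 | R4,200 | 1,500/0.05 = R30,000 |
| 60% v 50% | 3,600/0.60 = R6,000 | R4,200 | 1,500/0.10 = R15,000 |

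Real delivery costs widen the gap. At 60% v 50%, an assumed extra R1,000 per head gives an intervention average of 4,600/0.60 = R7,667 against 2,500/0.10 = R25,000 incremental. An assumed R3,000 gives 6,600/0.60 = R11,000 against 4,500/0.10 = R45,000.

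**2. How many count as improved without any effect of the workshops.** Baseline and endline scores were simulated as correlated normal values, rounded to integers and limited to the score range. With zero mean change the formula is P(increase) = (1 − P(tie))/2. Score ranges, means, SDs and correlations are assumptions, since the article gives none.

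- Fine-grained score (0–70, mean 42, SD 10 or 14, correlation 0.3–0.8): ties 3–6%, improved 47–49%. Example: SD 14, correlation 0.5, ties 3.3%, so (1 − 0.033)/2 = 48%.
- Coarse score (0–14, mean 8, SD 2 or 3, same correlations): ties 12–30%, improved 35–44%. Example: SD 2, correlation 0.8, ties 30%, so (1 − 0.30)/2 = 35%.
- Both arms rise equally by 0.2–0.5 SD (0–70, mean 40, SD 12, correlation 0.5 or 0.7): improved 56–72%, with no between-arm effect. The Background makes such a rise plausible, since the earlier cash-transfer pilot was associated with increased wellbeing.

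The share improved therefore depends heavily on the instrument and on any common rise, and neither reflects what the workshops add.

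**3. Where the reimbursement is booked.** At R1,500 per full attender, full attendance costs 120 × 1,500 = R180,000 for the planned arm, or 149 × 1,500 = R223,500 for the 149 intervention participants reported under Trial status. Of each R150, R50 is for transport, which the Economic evaluation section also estimates as a participant cost. If transport is counted there, 10 × R100 = R1,000 per full attender has no stated place in the costing.

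**The case against.** The strongest reply is that this is one secondary outcome of a pilot, that the article refers to an additional file for detail on outcomes, and that nothing is lost: costs by arm and scores by arm are the inputs to an incremental ratio. That stands as far as it goes, and it makes the repair cheap. It does not rescue the definition. The article does not leave the measure open. It fixes one, and that one does not address the objective. An unseen file would have to depart from the text to repair it.

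A reader might infer more than the documents support:

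- **Overheads shared with the control arm.** The residual rule for unlisted inputs might suggest that workshop payments will be loaded partly onto controls. The article does not say so. Workshop sessions are costed in detail, the breakdown is by arm, and step-down allocation could assign the payments to the workshops. What stands is that their place is not stated.
- **Regression to the mean.** Eligibility is not based on a wellbeing or depression score, so there is no reason to expect the group to drift upwards on that account. Measurement noise is enough for the point.
- **Unequal cash.** R1,500 is 71% of R2,100, but it covers transport and lunch as well as time. Only 10 × R50 = R500, or 24%, is described as being for time. The full sum cannot be read as extra cash income.
- **Transport and carer costs wrongly attributed.** Under a societal perspective they are costs whoever pays. Double counting is a risk only if the reimbursement is added on top.

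**Conclusion.** The point holds for the measure itself. A per-arm average cost per participant with any increase, on an unnamed score, cannot answer the cost-effectiveness objective or show what the workshops add to the same cash. That conclusion follows from the definition and needs no assumption.

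The size is illustrative. On documented payments, an ineffective programme yields R7,200 against R4,200 per improver, and a ten-point gain yields R6,000 against R4,200 where the incremental cost is R15,000. These figures rest on assumed proportions improved, full attendance and no other delivery cost. It would be too strong to say that about half improve by chance: this needs a fine-grained score and zero mean change. It would also be too strong to say that the trial cannot answer the question, since the planned data collection supports an incremental analysis. The silence on the R150 is a minor addition.

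**What to change.** - Define the cost-effectiveness measure as the between-arm difference in mean cost per participant divided by the baseline-adjusted between-arm difference in one wellbeing score, named in advance. The planned mixed model for endline scores already supplies the denominator.
- Give uncertainty that respects clinic clustering for both cost and effect. Report the two differences beside the ratio, because the ratio is unstable when the effect is near zero. The choice of interval method can be left to the analysts.
- Keep the per-arm averages as description. If a count of improvers is kept, state the instrument and the smallest rise that counts.
- Book the R150 per workshop explicitly to the workshops in the intervention arm, and count transport and carer costs once.

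The cost is revised wording and some extra analysis of data already being collected. The ratio will probably look less favourable than the averages, and with 10 clinics per arm its interval will be wide. Both are acceptable in a pilot meant to inform a larger trial.
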